# A randomised controlled trial to compare the efficacy, safety, and tolerability of low dose, short course primaquine in adults with uncomplicated *P*. *vivax* malaria in two hospitals in India

**DOI:** 10.1186/s13063-024-07987-0

**Published:** 2024-02-29

**Keywords:** *P. vivax*, Vivax malaria, Radical cure, Primaquine, Malaria elimination, Randomised controlled trial

## Abstract

**Background:**

*Plasmodium vivax* remains a major challenge for malaria control and elimination due to its ability to cause relapsing illness. To prevent relapses the Indian National Center for Vector Borne Diseases Control (NCVBDC) recommends treatment with primaquine at a dose of 0.25 mg/kg/day provided over 14 days. Shorter treatment courses may improve adherence and treatment effectiveness.

**Methods:**

This is a hospital-based, randomised, controlled, open-label trial in two centres in India. Patients above the age of 16 years, with uncomplicated vivax malaria, G6PD activity of ≥ 30% of the adjusted male median (AMM) and haemoglobin levels ≥ 8 g/dL will be recruited into the study and randomised in a 1:1 ratio to receive standard schizonticidal treatment plus 7-day primaquine at 0.50 mg/kg/day or standard care with schizonticidal treatment plus 14-day primaquine at 0.25 mg/kg/day. Patients will be followed up for 6 months. The primary endpoint is the incidence risk of any *P. vivax* parasitaemia at 6 months. Safety outcomes include the incidence risk of severe anaemia (haemoglobin < 8 g/dL), the risk of blood transfusion, a > 25% fall in haemoglobin and an acute drop in haemoglobin of > 5 g/dL during primaquine treatment.

**Discussion:**

This study will evaluate the efficacy and safety of a 7-day primaquine regimen compared to the standard 14-day regimen in India. Results from this trial are likely to directly inform national treatment guidelines.

**Trial registration:**

Trial is registered on CTRI portal, Registration No: CTRI/2022/12/048283.

## Administrative information

Note: the numbers in curly brackets in this protocol refer to SPIRIT checklist item numbers.

## Introduction

### Background and rationale {6a}

In 2021, there were an estimated 247 million cases of malaria from 84 malaria-endemic countries, out of which 4.9 million were caused by *Plasmodium vivax* [1]. India accounted for 79% of cases in the South East Asia (SEA) region and reported approximately 60,000 vivax malaria cases [1]. India along with Pakistan, Papua New Guinea and Ethiopia are the largest contributors to the global vivax burden [1]. There has been a considerable decrease in the malaria burden over the last 6 years since India launched its plan for malaria elimination in 2016; however, case numbers for of vivax malaria remain high. In 2022, the number of cases of vivax malaria increased to 74,126, accounting for 43% of all cases of malaria [2]. If India is to reach its target for malaria elimination in 2030, better strategies will be needed to address the *P. vivax* burden [3].

*P. vivax* is a substantial challenge for malaria control and elimination because of its ability to cause relapsing infections. Relapse results from the activation of dormant liver-stage hypnozoites and can occur weeks or months following an acute infection of vivax malaria [4]. Recurrent infections are associated with a febrile illness, an increased cumulative risk of severe anaemia, direct and indirect mortality, and are an important source of onward transmission of the parasite [4]. The only widely available hypnozoitocidal drug (capable of clearing the intra-hepatic hypnozoites of *P. vivax*) is primaquine. Primaquine is an 8-aminoquinoline compound with the potential of causing severe drug-induced haemolysis in glucose-6-phosphate-dehydrogenase (G6PD) deficient patients. Novel point-of-care tests for G6PD deficiency are now available [5] and they have the potential to facilitate the safer use of primaquine.

The Indian National Center for Vector Borne Diseases Control (NCVBDC) recommends primaquine for the radical cure of vivax malaria in the country. The guidelines recommend caution in areas with a known high prevalence of G6PD deficiency and patients are advised to stop the drug intake if adverse effects occur [6, 7]. To reduce the risk of drug-induced adverse effects, primaquine is recommended at a total dose of 3.5 mg/kg given over 14 days (0.25 mg/kg per day) [7]. However, this prolonged treatment is associated with poor compliance and therefore low effectiveness [8]. To ensure better adherence to the 14-day primaquine regimen, supervised administration of primaquine can be effective and considered to enhance compliance among patients with vivax malaria in India [9]. However, directly observed treatment will require additional costs. An alternative option to increase adherence is a shorter treatment regimen such as a 7-day primaquine course (0.5 mg/kg day over 7 days) which was recently endorsed by WHO [10].

There is limited evidence for the efficacy and safety of this shorter regimen from India and South Asia in general. Two studies have been conducted, one including a sustained release formulation of primaquine [11], and the other was conducted more than 10 years ago [12]. An individual patient data meta-analysis has demonstrated a lack of available evidence on optimal primaquine dosing in South Asia supporting the need for additional data on 7-day primaquine efficacy and safety in India [13].

Our open-label randomised trial aims to compare the efficacy, tolerability and safety of short-course, low-dose (0.50 mg/kg/day for 7 days) primaquine, with the current standard of care (0.25 mg/kg/day for14 days) to prevent *P. vivax* recurrences in India.

### Objectives {7}

To assess the 6-month efficacy of a 7-day course of primaquine treatment regimen (0.50 mg/kg/day) in preventing recurrent *P. vivax* parasitaemia in G6PD normal patients over 16 years of age compared to the current 14-day primaquine regimen (0.25 mg/kg/day)To assess the safety and tolerability of a 7-day course of primaquine treatment regimen compared to the current standard primaquine regimen.

### Trial design {8}

This is a randomised, controlled, non-inferiority, open-label trial in G6PD normal patients with uncomplicated *P. vivax* malaria comparing a shorter duration primaquine regimen to the current standard primaquine treatment to prevent vivax recurrence.

## Methods: participants, interventions and outcomes

### Study settings {9}

Two sites have been selected in India. The first site is Calcutta National Medical College, Kolkata, West Bengal and the second site is Ahmedabad Municipal Corporation Hospital, Ahmedabad, Gujarat.

### Eligibility criteria {10}

#### Inclusion criteria

The participant may enter the study if all of the following apply:*P. vivax* (asexual) malaria mono-infection confirmed by microscopy on a thick or thin blood smear.Age 16 years and over of either genderFever > 37.5 °C axillary, or a history of fever within the previous 48 h.Female patients of child-bearing potential will be included if non-lactating and willing to use contraceptive methods during the study period. Non-child-bearing potential is defined as:Post-menopausal (12 months of spontaneous amenorrhea or 6 months of spontaneous amenorrhea with serum FSH > 40 mIU/mL), pre-menopausal and has had a hysterectomy or a bilateral oophorectomy or a bilateral tubal ligation with medical report verification or,Child-bearing potential, has a negative urine pregnancy test at screening, and agrees to comply with one of the following during the treatment stage of the study and for a period of 90 days after stopping the study drug:Use of oral contraceptive, either combined or progesterone alone (if no contraindications to oral contraceptives exist).Barrier contraceptive if oral contraceptives are contraindicated.Use of an intrauterine device.Willing to give informed consent.Willing to comply with protocol instructions and duration of follow-up.Living in and around the site facilities (to facilitate follow-up).

#### Exclusion criteria

The participant may not enter the study if any of the following apply:Patients with G6PD activity less than 30% of the adjusted male median (AMM), tested by UV spectrophotometry.Patients with mixed infection with *P. vivax* and *P. falciparum* (e.g. identified by Giemsa-stained smear or rapid diagnostic test).Patients with dengue coinfection (detected by dengue NS1 antigen rapid test).Patient with body weight less than 40 kg.Severe *P. vivax* malaria is defined as per National Guidelines [6] and WHO^9^ criteria.Haemoglobin <8 g/dL.History of haemolytic episodes or haemolytic anaemia or methaemoglobinemia or blood transfusion within the past 90 days.Unable to tolerate oral treatment.Pregnant and lactating women.Known allergy to chloroquine, primaquine or any other related drugs.Evidence of gastro-intestinal dysfunction that could alter absorption or motility (e.g. diarrhoea defined as >3 episodes of watery stools in the previous 24 h or patients who have had three episodes of vomiting within 24 h prior to screening).Use of concomitant medications that could induce haemolysis or haemolytic anaemia or depressants of myeloid element of the bone marrow.Any antimalarial treatment taken during 1 month prior to screening.Ongoing prophylaxis with drugs having antimalarial activity.Participation in any other investigational drug study of within 3 months prior to screening.Any other underlying disease that would require hospitalisation and could compromise the diagnosis and the evaluation of the response to the study medication (including clinical symptoms of immunosuppression, HIV, hepatitis, tuberculosis, splenectomy conducted earlier as confirmed by history or clinical examination; evidence of clinically significant cardiovascular, pulmonary, metabolic, gastrointestinal, neurological, or endocrine diseases, malignancy, or other abnormalities).Retinal/visual field defects or auditory defects and history of psoriasis and porphyria. Subjects meeting any of the exclusion criteria will not be enrolled in the study and treated according to NCVBDC Guidelines.

### Who will take informed consent? {26a}

Patients attending the hospitals at either study site will be screened for enrolment into the trial. On screening day (Day − 1), the patients will be provided with a brief written consent outlining the screening tests to be conducted and once a patient qualifies for enrolment, a complete informed consent process will be initiated before enrolment (Day 0). The informed consent describing the purpose of the study, the procedures to be followed, and the risks and benefits of participation will be sought from the participants prior to enrolment. The age of consent will be considered as ≥ 18 years. For participants between the age of 16–18, written assent will be obtained. The signed written informed consent will be obtained by trained and authorised staff from each subject prior to enrolment in the study. For adolescents who are not legally able to give consent, written informed consent is obtained from their Legally Authorised Representative (LAR) in accordance with applicable laws or regulations. All interviews will be conducted in the native language (Gujarati, Bengali or Hindi) of the patients by the study staff. If a patient, parent or guardian is unable to read or write, a signature from a witness to the informed consent discussion will be obtained. Patients/parents or guardians will be informed that participation in the study is completely voluntary and that they may withdraw from the study at any time.

### Additional consent provisions for collection and use of participant data and biological specimens {26b}

All patients will be asked to provide consent for the long-term storage of blood samples in form of dried blood spots (DBS) for molecular analysis of the parasite. Furthermore, patients are informed about the use of their health data for current and any further research in relation to it at enrolment.

#### Interventions

This trial consists of two arms:Intervention arm: 0.50 mg/kg/day primaquine for 7 days (3.5 mg/kg total dose)Control arm: 0.25 mg/kg/day primaquine for 14 days (3.5 mg/kg total dose)

Additionally, all participants in both arms will receive blood schizonticide treatment, i.e. chloroquine (total dose 25 mg base/kg) as per NCVBDC guidelines [6, 7]. All chloroquine doses will be directly supervised.

All patients will be tested initially, and those found to be G6PD deficient (defined as < 30% of AMM) will be excluded from this randomised study but will receive medical care according to WHO guidelines: 0.75 mg/kg/week for 8 doses (total dose 6 mg/kg).

### Explanation for the choice of comparators {6b}

All participants in the control arm will be treated with radical cure for acute uncomplicated vivax malaria according to local NCVBDC guidelines [6, 7]: 0.25 mg/kg bodyweight primaquine for 14 days, starting on enrolment (Day 0). If the participant vomits the treatment within 60 min, a repeat dose will be administered. If the patient vomits the second dose, he or she will receive parenteral therapy with artesunate and will be withdrawn from the study. Primaquine treatment will be observed daily on the first 3 days, and then alternatively up to 14 days by home visits by staff. Primaquine will be administered with food, to help reduce gastrointestinal side effects.

### Intervention description {11a}

Patients in the intervention arm will be treated with a 3 day regimen of chloroquine (total dose 25 mg base/kg) plus primaquine (0.50 mg/kg bodyweight for 7 days). If the participant vomits the treatment within 60 min, a repeat dose will be administered. If the patient vomits the second dose, he or she will receive parenteral therapy with an artemisinin combination therapy (ACT) and be withdrawn from the study. Primaquine treatment will be observed daily on the first 3 days, and then on alternate days up to 7 days by home visits by staff. Primaquine will be administered with food, to help reduce gastrointestinal side effects.

### Criteria for discontinuing or modifying allocated interventions {11b}

Each participant has the right to withdraw from the study at any time. If the participant withdraws consent, uses antimalarial drugs outside of the study protocol, or who fails to attend a follow-up visit and is unable to be located within 48 h on days 1–14 or for more than 2 subsequent visits post day 14, the patient will be excluded/withdrawn. It will be left to the investigator’s clinical judgment whether or not an adverse event (AE) is of sufficient severity to require stopping the participant’s treatment. If the participant is withdrawn due to an AE, the investigator will arrange for follow-up visits or telephone calls until the AE has resolved and conditions stabilised.

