### Strategies to improve adherence to interventions {11c}

Patients of both arms will be visited at home by study staff on alternate days and provided with medication for 2 days. On the day of visit, primaquine doses will be observed and the patient is advised to take treatment on the following day. The patient will also be asked about the previous day’s dose. If patients are not found/located, all efforts will be made to ensure that they restart treatment.

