### Sample size {14}

The 0.25mg/kg/day × 14 days regimen of primaquine is associated with ~13% recurrence rate of vivax malaria [12]. The present study will assess if 0.50 mg/kg/day for 7 days will have an equivalent recurrence rate within a margin of 10%. A sample size of 200 per group, assuming a 30% loss to follow-up at 5% significance will provide 68% power to detect this difference. Accordingly, we have decided on 200 patients at each site (100 in each arm), 400 in total.

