Day 2: All participants will be reviewed and patients in both arms will receive their third dose of primaquine treatment under observation. Finger prick blood sample will be collected for haemoglobin measurement and microscopy. Physical examination of urine will be conducted.

Days 3–6: Participants in both arms will be treated with primaquine. Home visits will be conducted on alternate days and primaquine doses will be given for that day and the following day for both arms.

Day 7: The study team will visit the participant at home. A brief physical examination will be conducted by a Study Nurse. Finger prick blood sample will be collected for haemoglobin measurement and microscopy. Physical examination of urine will be conducted.

Days 8-13: Participants in the control arm will be treated with primaquine. Home visits will be conducted on alternate days and primaquine doses will be given for that day and the following day for the control arm. No interaction with patients in the intervention arm.

Days 14, 21, and 28 and months 2, 3, 4, 5, and 6: The study team will visit participants at home where they will be reviewed. A brief physical examination will be conducted by the Study Nurse. Finger prick blood sample will be collected for haemoglobin measurement and microscopy.

Unscheduled Visit: All participants with fever or symptoms indicative of malaria will be asked to return to the same health centre as on enrolment. A symptom questionnaire will be completed, a brief physical examination undertaken, and a venous blood sample will be collected and a malaria smear prepared for malaria diagnoses (read immediately) and CBC including haemoglobin and LFT measured. Physical examination of urine will be conducted. In patients with recurrent parasitaemia, DBS will be made and stored for parasite analysis.

Demographics: The patient’s date of birth (or if not known, the estimated age) and gender will be recorded. For screening purposes and if the patient is a female of childbearing age, she will be asked if she is currently pregnant, lactating, planning to get pregnant and the date of the first day of her last menstrual period.

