## Statistical methods

### Statistical methods for primary and secondary outcomes {20a}

#### Efficacy analyses

The efficacy analyses will be based on the modified intention to treat population. Time to first recurrent vivax parasitaemia will be used to compute the Kaplan-Meier estimates of risk of *P. vivax* recurrence at month 6 for treatment arms and control arms with primaquine for each study site. Also, the comparison of the relative hazards between trial arms (hazard ratio (95% confidence interval)) will be estimated from a Cox regression model for the time to the first recurrent episode.

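### Withdrawal rules end parasite follow-up, not only study drug, for patients lost for reasons that may depend on treatment and prognosis, which can bias the non-inferiority comparison

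*Protocol article*

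**What the plan says.** All references are to the protocol article.

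- **Design.** Trial design {8} describes a "randomised, controlled, non-inferiority, open-label trial".
- **Vomiting.** The sections on choice of comparators {6b}, intervention description {11a} and rescue treatment all remove a patient after a second vomited dose. In {11a} the patient is to receive other therapy "and be withdrawn from the study".
- **Other antimalarials and missed visits.** Section {11b} covers anyone who withdraws consent, uses antimalarials outside the protocol, or "who fails to attend a follow-up visit and is unable to be located within" 48 h on days 1 to 14, or for more than two subsequent visits after day 14. For all of them, "the patient will be excluded/withdrawn".
- **After withdrawal.** Section {11b} provides visits or calls only for patients withdrawn because of an adverse event, until it has resolved. No slides or haemoglobin to month 6 are mentioned for any withdrawn patient.
- **Analysis.** "The efficacy analyses will be based on the modified intention to treat population", with Kaplan-Meier and Cox on time to first recurrent parasitaemia.
- **Outcome definition.** Outcomes {12} makes not having taken another drug with antimalarial activity a condition of recurrence-free efficacy.
- **Sample size {14}.** The 14-day "regimen of primaquine is associated with ~13% recurrence rate of vivax malaria". The margin is 10%, loss to follow-up 30%, and power 68% with 200 per arm.

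**The concern.** Leaving the drug and leaving the study are treated as one event. Vomiting is a tolerability outcome of this trial, and the daily dose is 0.50 mg/kg in one arm and 0.25 mg/kg in the other, so the number withdrawn for it may differ by arm. A patient who vomits doses, vanishes or self-treats may also have a different risk of recurrence, and self-treatment may itself be the sign of one. If slides stop at that point, the month-6 outcome does not exist and no analysis plan can restore it.

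In a non-inferiority trial, loss of the patients most likely to fail can shrink a real difference and let an inferior regimen pass. Censoring does not cure this, because Kaplan-Meier and Cox assume that a censored patient has the same later risk as those still followed. A second vomited dose falls within the first two weeks of a 6-month follow-up, so censoring there is close to deletion.

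The status in {11b} also joins two things with different consequences: exclusion would take a patient out of the analysis, and withdrawal would stop follow-up but keep the data to date.

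**Working it through.** **1. The plan's own figure.** Inputs from Sample size {14}: 13% recurrence, taken as equal in both arms; margin 0.10; 200 × 0.7 = 140 per arm. The sidedness of the 5% level is not stated; one-sided 2.5% is assumed.

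Farrington-Manning: the null-restricted risks are 0.0947 and 0.1947.
- Null SE = √[(0.0947×0.9053 + 0.1947×0.8053)/140] = 0.0416
- Alternative SE = √[2×0.13×0.87/140] = 0.0402
- Power = Φ[(0.10 − 1.96×0.0416)/0.0402] = 67.7%

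This reproduces the stated 68% (an unpooled Wald test gives 70.1%). The point does not rest on a wrong power figure.

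**2. Effect of outcome-related loss.** True risks are set at the margin: control 0.13, 7-day 0.23. A fraction L of an arm is lost, and lost patients have RR times the recurrence risk of retained patients. L by arm and RR are assumptions, because the article gives neither. Lost patients are left out entirely.

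- Observed risk = true risk / [(1 − L) + L×RR]
- False non-inferiority rate = Φ[(0.10 − d)/SE − 1.96], where d is the observed difference and SE is the unpooled SE with 200×(1 − L) per arm

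Example, RR 2, 5% control and 10% 7-day lost:
- control 0.13/1.05 = 0.1238; 7-day 0.23/1.10 = 0.2091; d = 0.0853
- SE = √[0.1238×0.8762/190 + 0.2091×0.7909/180] = 0.0386
- Φ(0.381 − 1.96) = 5.7%

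Example, RR 2, 30% lost in each arm:
- control 0.13/1.30 = 0.1000; 7-day 0.23/1.30 = 0.1769; d = 0.0769
- SE = √[(0.1000×0.9000 + 0.1769×0.8231)/140] = 0.0410
- Φ(0.563 − 1.96) = 8.1%

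| Lost, control / 7-day | RR | Observed difference (true: 10 points) | False non-inferiority |
|---|---|---|---|
| 30% / 30% | 1 | 10.0 | 2.5% |
| 5% / 10% | 2 | 8.5 | 5.7% |
| 30% / 30% | 1.5 | 8.7 | 4.9% |
| 30% / 30% | 2 | 7.7 | 8.1% |
| 30% / 30% | 3 | 6.3 | 16.8% |
| 20% / 30% | 2 | 6.9 | 11.8% |
| 30% / 20% | 2 | 9.2 | 4.0% |

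**3. Direction.** Now let the true risk be 13% in both arms, with RR 2. With 20% control and 30% 7-day lost, the observed risks are 0.13/1.2 = 10.8% and 0.13/1.3 = 10.0%, which is 0.8 points in favour of the 7-day arm. With the losses reversed, it is 0.8 points against it.

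**4. Other antimalarials, sections side by side.** Under {11b} the user is removed. Under Outcomes {12} the same user is not recurrence-free. Under Efficacy analyses {20a} only parasitaemia is an event, so a user without a positive slide has none. Section {11d} merely records the use. These are different handlings of one patient in the primary outcome.

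**The case against.** The strongest reply is that withdrawal from the study is not shown to mean removal from the analysis. The modified intention-to-treat set is not defined in the article, and time-to-event methods can keep a patient up to the last slide. That stands, and it is why the problem is informative censoring rather than proven deletion. The table leaves lost patients out entirely, so it overstates the effect for those censored late.

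It is also fair that no arm-specific loss, and no risk among the lost, is documented. The 30% covers all loss, not only loss imposed by these rules.

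Four stronger readings are tempting but unsupported:

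- **That the rules favour the 7-day arm.** Intolerance may remove more patients on the higher daily dose, but missed-visit losses may fall more on control. No net direction is shown.
- **That the lack of a per-protocol analysis is a defect.** Such a set, and the definition of the modified set, commonly sit in the full protocol or SAP, which are not shown.
- **That the missed-visit rule falls harder on control.** For days 8 to 13 the procedures say "No interaction with patients in the intervention arm". But Table 1 gives both arms the same assessment visits within days 1 to 14 (days 1, 2, 7 and 14), and the article does not say that control dosing visits count as follow-up visits.
- **That {11b} contradicts {11c}**, where for unlocated patients "all efforts will be made to ensure that they restart treatment". The two can be read in sequence: search first, then withdraw after 48 h.

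**Conclusion.** The concern holds as a fault of conduct, not as demonstrated bias. The article ends parasite follow-up for reasons that may depend on treatment and prognosis, and it states no month-6 outcome collection for these patients. An SAP can decide how to treat missing outcomes, but it cannot supply slides that were never taken.

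If lost patients have twice the risk of retained ones and true risks lie at the margin, the error rate rises from 2.5% to about 5.7% (5% v 10% lost) or 8.1% (30% lost per arm). It does not rise if loss is unrelated to outcome. These figures show what is possible; they do not predict this trial. The conflicting handling of other antimalarial use stands without any such assumption.

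**What to change.** 1. State in {6b}, {11a}, {11b} and the rescue section that stopping study drug, or receiving other treatment, does not end follow-up. Continue slides, haemoglobin and adverse event collection on the Table 1 schedule to month 6 unless consent is withdrawn.
2. Replace the combined status in {11b} with a single one: retained, and censored at the last slide only if no further data can be obtained. Keep these patients in the efficacy set as randomised.
3. Reconcile {11b} with Outcomes {12}: state once how use of another antimalarial counts in the primary outcome, including when it was given under the protocol's own rescue rule.
4. Reconcile the accounts of treatment after a second vomited dose. Section {6b} and the rescue section name parenteral artesunate, while {11a} names a parenteral artemisinin combination therapy. The choice is a clinical matter for the sponsor.

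The cost is a short amendment and some extra follow-up. The visits already stand in Table 1: a patient withdrawn before day 14 would have at most eight from then on (days 14, 21 and 28, and months 2 to 6), plus any left in the first two weeks. Patients who truly cannot be found will still be lost, so the change reduces the problem without removing it.
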